## Methods

### Objectives

The trial will evaluate the potential benefits of US on early childhood development and child care by augmenting a routine antenatal service currently provided mainly in tertiary public health facilities in South Africa, with plans to be rolled out to district hospitals. The goal of the intervention is to increase parental investment not only in child survival, but also for the well-being and healthy growth and development of their child. We aim to establish whether, compared to routine care, messages about fetal and child development delivered during one (< 25 weeks) or two (< 25 weeks and again < 36 weeks) fetal USs improve ECD and growth, exclusive breastfeeding, mother/father–infant attachment, maternal and paternal well-being, father involvement and prenatal and postnatal clinic attendance.

Specific objectives are to evaluate whether child development messages delivered during one or two USs:
Improve early child developmentImprove infant breastfeeding practices and healthy child growthImprove parent–infant attachment and interaction during pregnancy and 6 months after birthIncrease paternal engagement in a young child’s development and care

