### Design

Eligible mothers will be randomised to one of three arms: Arm 1, the control group, will receive standard practice of care during pregnancy; Arm 2 will receive the child development intervention at the first research ultrasound visit; and Arm 3 will receive the intervention at two research ultrasound visits. All mothers, infants and partners (where available) will be followed-up 6 weeks and 6 months postnatally for assessments. Participants will continue to receive routine antenatal, perinatal and postnatal care as provided by the tertiary care facility from which all participants are being recruited.

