### Intervention

Women will be randomised to one of three arms on recruitment at CHBH < 25 weeks gestation after having a fetal ultrasound examination as part of routine antenatal hospital services. The women will be blind to their arm allocation and remain blinded until study completion. Using computer-generated simple randomisation, each consecutive woman screened will be randomly allocated to a study arm. Research assistants responsible for screening will receive the study arm numbers for allocation from the study coordinator on a daily basis. The allocation sequence will be concealed from the research assistants enrolling the participants. Women recruited for Arm 1 will act as the control group and will receive one further standard US at DPHRU < 25 weeks gestation, when they will receive standard fetal growth measurements but no child development messages.

In addition to their routine antenatal US at CHBH, women recruited to Arm 2 will receive an additional US < 25 weeks gestation at DPHRU, during which they will receive messages to promote early childhood development. During the US session, the sonographer will talk with the mother and partner, if present, about the fetus’ sensory development and capacity for learning, fetal responsivity to the environment, maternal well-being and the dependence of the fetus on maternal and paternal health and well-being before and after birth.

In addition to their routine antenatal US at CHBH, women recruited to Arm 3 will receive two additional USs at DPHRU, one < 25 weeks gestation (early US) and another < 36 weeks gestation (late US). They will receive the same child development messages as mothers in Arm 2 at the first US. During the second US, in addition to childhood development messages, the sonographer will encourage the woman and her partner, if present, to personalise the baby, strengthen intentions to exclusively breastfeed, talk and sing to the child before and after birth, and counsel them on how to respond to their young infant’s emotional and learning needs.

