Partner involvement and interest in the baby is encouraged by inviting partners to attend the ultrasound sessions of women in all three arms. For mothers recruited to Arms 2 and 3, digital ultrasound images and a photograph of the woman (with her partner where present) having the US will be sent to parents via WhatsApp and printed images given to the parents. A small baby book with the child development messages, as appropriate to the arm, is given to the mothers in Arms 2 and 3, and they are encouraged to paste the printed pictures into the book and to share the US images and photographs with family and friends.

Two qualified and registered sonographers will be trained to deliver the intervention and a Philips HD9 Ultrasound System will be used to conduct all USs. Due to the nature of the intervention, the sonographers will not be blind to the mother’s arm allocation.

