### Formative and process data

Study procedures were informed by formative qualitative research conducted with pregnant women attending antenatal care at CHBH prior to the trial inception. We have written standard operating procedures (SOPs) to support the research team to deliver the study procedures and intervention according to the protocol. Participant adherence will be assessed by counts (e.g., visit attendance) and intervention delivery will be monitored by observing contacts between the sonographer (who will conduct the US and deliver the ECD messages) and participants (intervention and control) to record the nature of interactions. We will monitor intervention dose and experience by recording the duration of the ultrasound visit (with and without delivery of the intervention) and by gathering participant and partner views on the ultrasound experience. Ongoing consultation with a key stakeholder network will inform intervention procedures and assist with contextualising the intervention and addressing any challenges that may arise during trial implementation.

Due to the well-documented challenges with engaging men in research and health care in South Africa [54], we will adopt pro-active recruitment strategies, which will include telephone calls to partners after participant enrolment and follow-up calls closer to the visit to encourage attendance. We have also included Saturday sessions for those partners who are unable to attend during the week due to work commitments. Research staff will make regular contact with participants in-between study visits to maintain the accuracy of records and to promote retention of participants in the study. We will follow-up participants who default and those who withdraw to gain an understanding of why they dropped out during the course of the trial.

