## Discussion

While ultrasound examination has long been regarded as having potential to be transformative and to improve parental behaviour [14], as well as commitment to the growing child [12], this hypothesis has only been tested in a few studies in high-income countries, fewer of which were randomised control trials [55].

There is clear evidence from high-income countries that the first time a prospective mother sees an image of their fetus during US is an emotionally enjoyable experience, which parents report intensifies their attachment to the coming baby. This is true also of prospective fathers [22, 56], and is reported as being an important bonding experience for the family [57]. A number of studies have examined the impact of ultrasound examination on maternal attachment [24, 58, 59]. However, women’s experiences of US are dependent on the context and the behaviour of the sonographer, with some women reporting feeling objectified and poorly informed during the experience [60].

Research on the emotional and relationship effects of early US are important because maternal (and presumably paternal) representations of the coming baby are significant predictors of parent–infant interactions which, in turn, affect healthy infant development [61, 62]. A recent review of interventions indicated that awareness programmes, most commonly involving pregnancy US, were amongst the most promising interventions to increase parent–fetal attachment [55]. There is agreement that studies are needed which follow up parental–child behaviour and healthy child development postnatally, include fathers and examine the construct in a wider diversity of settings, including in low and middle-income countries. Testing the added benefits of pregnancy US for child development is the gap that this proposed randomised control trial in South Africa seeks to address.

Should this trial demonstrate feasibility and improvement in the specified intermediate and outcome measures, the next step would be a pragmatic trial situated in the health-care system, with longer-term outcomes and cost-effectiveness estimations.

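### The comparator is called routine care, but Arm 1 is routine care plus an extra research scan, so no effect over routine care alone can be estimated

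*Protocol article*

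**What the plan says.** The aim in the Objectives section of the protocol article reads "We aim to establish whether, compared to routine care, messages about fetal and child development delivered during one" or two scans improve development, growth, feeding, attachment and clinic use. The Background paragraph of the Abstract names the same comparator. The Design section says "Arm 1, the control group, will receive standard practice of care during pregnancy".

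The Intervention section describes something else: "Women recruited for Arm 1 will act as the control group and will receive one further standard US at DPHRU", at which fetal growth is measured and no messages are given. The Methods paragraph of the Abstract agrees with this. Partner involvement is encouraged by "inviting partners to attend the ultrasound sessions of women in all three arms". The section on formative and process data adds recruitment efforts aimed at fathers, "which will include telephone calls to partners after participant enrolment", without restricting them to particular arms.

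On ultrasound itself, the Objectives open with "The trial will evaluate the potential benefits of US on early childhood development and child care by augmenting a routine antenatal service", and the Discussion says "Testing the added benefits of pregnancy US for child development is the gap that this proposed randomised control trial" addresses. The Abstract's Discussion paragraph makes the same statement. The list of aims that follows in the Objectives is worded around messages: "Specific objectives are to evaluate whether child development messages delivered during one or two USs" improve four groups of outcomes.

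**The concern.** The sentences that state the aim and label the control arm do not match the account of what that arm receives. A report that follows the aim would present Arm 2 or Arm 3 against Arm 1 as an effect over routine care, and the trial has no arm from which that effect can be estimated.

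The difference may matter on the protocol's own rationale. The Background cites studies in which scans raised parental attachment and gave an opportunity to engage fathers. If an extra scan or a partner invitation has any effect, Arm 1 benefits from it too. A null result could then be misreported as no benefit over routine care. A positive Arm 3 result could be credited to scanning, because the general statements in the Objectives and Discussion speak of the benefits of ultrasound.

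**Working it through.** **Step 1. The plan's own figure.** Inputs: a 0.5 SD difference between arms, 90% power and 15% attrition (Recruitment section); two-sided 0.05 (Data analysis section).

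- n per arm = 2 × (1.960 + 1.282)² / 0.5² = 2 × 10.507 / 0.25 = 84.06, rounded up to 85. The t-test version gives 85.03.
- With attrition: 85 / (1 − 0.15) = 100 per arm; 3 × 100 = 300.

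The stated 85, 100 and 300 are reproduced. The 0.5 SD is a difference between arms, so it already refers to the contrasts that are randomised.

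**Step 2. What each arm receives** (Intervention section and the Methods paragraph of the Abstract).

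| | Routine care with hospital scan | Extra research scans | Messages | Images, photograph, baby book | Partner invited |
|---|---|---|---|---|---|
| Routine care alone (no such arm) | yes | 0 | none | no | no |
| Arm 1 | yes | 1 | none | no | yes |
| Arm 2 | yes | 1 | one session | yes | yes |
| Arm 3 | yes | 2 | two sessions, the second with added content | yes | yes |

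The first row is the comparator named in the aim. It differs from Arm 1 by one research scan and the partner invitation.

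**Step 3. What each contrast varies.**

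- Arm 2 − Arm 1: the number of scans is equal (1 − 1 = 0). The arms differ by messages, images, photograph and book. This isolates the one-visit message package.
- Arm 3 − Arm 1: one more scan (2 − 1 = 1), two message sessions and the materials. Scan and messages change together.
- Arm 3 − Arm 2: one more scan (2 − 1 = 1) and a second session with new content. Again both change together.
- Any arm − routine care alone: not available.
- Scan against no scan with messages held fixed: not available.

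**Step 4. The link to routine care.** By identity, (Arm 2 − routine care) = (Arm 2 − Arm 1) + (Arm 1 − routine care). The trial estimates the first term on the right. The second is not observed, and the documents give no figure for it.

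**The case against.** The strongest reply is that the extra control scan is a strength. It matches Arms 1 and 2 on scanning, so their difference can be attributed to the message package. With a control on routine care alone, messages would have been confounded with an added scan. This stands in full. A reader might infer that nothing the trial set out to learn can be concluded; the documents do not support that, because the specific objectives concern messages delivered during scans and Arm 2 against Arm 1 addresses them directly.

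The sentence on the benefits of ultrasound can also be defended. The Objectives qualify it as augmenting a routine service, the Background describes ultrasound augmented with messages and hypothesises about that combination, and no objective or analysis proposes to isolate scanning. So it would go too far to say that the trial fails a declared aim of isolating ultrasound. The sentences in the Discussion and in the Abstract's Discussion paragraph lack the qualifier, however, and should be aligned.

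Three further inferences are tempting and fail:

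- *Lost power.* This would require the 0.5 SD to be an effect over routine care, part of which the control arm shares. The Recruitment section defines it as a difference between arms, and the documents give no shared fraction.
- *Partner contact in all arms as a flaw.* Equal contact protects retention and comparability. The randomised contrast for paternal engagement is still valid.
- *A mismatch with roll-out.* The roll-out mentioned in the Objectives is of the routine scanning service. Delivery within the health system is left to a later pragmatic trial.

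The evidence that an extra scan is active is also mixed. The Background reports a review that found no evidence that seeing the fetus increases attachment, and a large cluster trial that suggested no increase in antenatal attendance. Finally, the Abstract and the Intervention section do disclose the extra control scan. That limits the harm but does not correct the sentences that state the aim and label the control.

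**Conclusion.** The comparator is wrong as written in the Abstract's Background, the Objectives and the Design section. Arm 1 is routine care plus one additional standard research scan without messages, with partner invitation. The trial therefore cannot estimate an effect over routine care alone, and no contrast isolates ultrasound. It can estimate the one-visit message package (Arm 2 against Arm 1) and a two-visit package whose second scan and messages cannot be separated (Arm 3 against Arm 1).

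The gap between Arm 1 and routine care has no size that can be taken from the documents. If the extra scan helps, which is an assumption, the difference from Arm 1 understates the benefit over routine care; if it has no effect, the two coincide. The validity of the randomised comparisons and the sample size are untouched. This is an error in what is claimed, correctable by wording, and not a failure of the design.

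**What to change.** 1. In the Abstract's Background, the Objectives and the Design section, name the comparator as routine care plus one additional standard research scan without messages, with partner invitation.
2. Define the estimands, using the arm numbers of the Design section, as the one-visit message package (Arm 2 against Arm 1) and the two-visit message package (Arm 3 against Arm 1), each against that control, and list the images, photograph and book as part of the package.
3. In the Abstract's Discussion paragraph, the Objectives and the Discussion, reword the general statements on the benefits of ultrasound as benefits of ultrasound augmented with messages.
4. State that neither the effect over routine care alone nor the effect of ultrasound alone is estimated, and carry this into the report's conclusions.

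The cost is a narrower claim. Trial conduct and the sample size do not change. The Trial status section records that recruitment is complete, but the wording can still govern analysis and reporting.

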### Design

Eligible mothers will be randomised to one of three arms: Arm 1, the control group, will receive standard practice of care during pregnancy; Arm 2 will receive the child development intervention at the first research ultrasound visit; and Arm 3 will receive the intervention at two research ultrasound visits. All mothers, infants and partners (where available) will be followed-up 6 weeks and 6 months postnatally for assessments. Participants will continue to receive routine antenatal, perinatal and postnatal care as provided by the tertiary care facility from which all participants are being recruited.

### Setting

The study is situated in Soweto, South Africa. Soweto is adjacent to Johannesburg and is the most populous Black urban residential area in South Africa, with over 1.3 million people counted in the most recent census [43]. Participants will be recruited from women attending antenatal care at Chris Hani-Baragwanath Academic Hospital (CHBH), a tertiary teaching hospital that attends to over 22,000 births annually. Women are referred to CHBH from community health centres with risk factors including HIV and hypertension. Recruited women will attend their study ultrasound visits at the SAMRC Development Pathways for Health Research Unit (DPHRU), which is located on the grounds of CHBH and in walking distance of the CHBH antenatal services.

### Procedures

#### Recruitment

Approximately 500 women present to CHBH each month for their first pregnancy US, of which 50% are < 25 weeks gestation. This offers a potential pool of 250 women per month to be included in the study. Participants will be recruited from women attending the Foetal Medicine Unit (FMU) at CHBH, where routine fetal ultrasound examinations are conducted. Eligible women will be resident within Soweto, aged 18 years and older, with a singleton pregnancy and presenting < 25 weeks gestation. Major fetal abnormalities detected during the first routine ultrasound examination conducted by an experienced radiologist in the FMU, or severe maternal morbidities, will exclude a pregnant woman from the trial. These women will be transferred to specialised clinical services at CHBH, where she will receive appropriate treatment.

Sample size calculations were based on detecting a 0.5-standard deviation (SD) difference between arms on both the Bayley III Language and Cognitive Scales, and *z*-scores for weight-for-age (WAZ), length-for-age (LAZ) and weight-for-length (WLZ) measured at 6 months of age at 90% power, which is 85 per arm. Allowing for 15% potential attrition during pregnancy and during follow-up to 6 months of infant age, the sample size in each of the three arms will be 100. This makes a total sample size of 300 women for recruitment.

### Intervention

Women will be randomised to one of three arms on recruitment at CHBH < 25 weeks gestation after having a fetal ultrasound examination as part of routine antenatal hospital services. The women will be blind to their arm allocation and remain blinded until study completion. Using computer-generated simple randomisation, each consecutive woman screened will be randomly allocated to a study arm. Research assistants responsible for screening will receive the study arm numbers for allocation from the study coordinator on a daily basis. The allocation sequence will be concealed from the research assistants enrolling the participants. Women recruited for Arm 1 will act as the control group and will receive one further standard US at DPHRU < 25 weeks gestation, when they will receive standard fetal growth measurements but no child development messages.

In addition to their routine antenatal US at CHBH, women recruited to Arm 2 will receive an additional US < 25 weeks gestation at DPHRU, during which they will receive messages to promote early childhood development. During the US session, the sonographer will talk with the mother and partner, if present, about the fetus’ sensory development and capacity for learning, fetal responsivity to the environment, maternal well-being and the dependence of the fetus on maternal and paternal health and well-being before and after birth.

In addition to their routine antenatal US at CHBH, women recruited to Arm 3 will receive two additional USs at DPHRU, one < 25 weeks gestation (early US) and another < 36 weeks gestation (late US). They will receive the same child development messages as mothers in Arm 2 at the first US. During the second US, in addition to childhood development messages, the sonographer will encourage the woman and her partner, if present, to personalise the baby, strengthen intentions to exclusively breastfeed, talk and sing to the child before and after birth, and counsel them on how to respond to their young infant’s emotional and learning needs.

Partner involvement and interest in the baby is encouraged by inviting partners to attend the ultrasound sessions of women in all three arms. For mothers recruited to Arms 2 and 3, digital ultrasound images and a photograph of the woman (with her partner where present) having the US will be sent to parents via WhatsApp and printed images given to the parents. A small baby book with the child development messages, as appropriate to the arm, is given to the mothers in Arms 2 and 3, and they are encouraged to paste the printed pictures into the book and to share the US images and photographs with family and friends.

Two qualified and registered sonographers will be trained to deliver the intervention and a Philips HD9 Ultrasound System will be used to conduct all USs. Due to the nature of the intervention, the sonographers will not be blind to the mother’s arm allocation.

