### Data collection

Study data will be collected and managed using REDCap (Research Electronic Data Capture) hosted by the University of the Witwatersrand. Data will be collected on the enrolled women, child and partners (where appropriate) at three stages: stage one, baseline at first research ultrasound visit at DPHRU < 25 weeks; stage two, 6-week postnatal follow-up; and stage three, 6-month postnatal follow-up. Data will be collected on tablets at stages one and two by two trained data collectors under the supervision of the study coordinator. At stage three, data will be collected by occupational therapists or physiotherapists trained in administering child development measures, under the supervision of the study coordinator. All data collectors will be trained on the principles of research ethics, Good Clinical Practice, referral procedures and management of difficult situations in the field.

Table 1 presents the schedule of enrolment, interventions and data collection.

**Table 1 Tab1:** Standard Protocol Items: Recommendations for Interventional Trials (SPIRIT) schedule of enrolment, interventions and data collection

	Study period				
	Enrolment	Intervention		Follow-up	
Timepoint	< 22 weeks GA	< 25 weeks GA	< 36 weeks GA	6 weeks postnatally	6 months postnatally
Enrolment					
Eligibility screen	X				
Informed consent	X				
Random allocation	X				
Interventions					
Early US		X			
Early US with messages		X			
Early and late US with messages		X	X		
Assessments: baseline and antenatal					
Socio-demographic questionnaire	X				
Fetal growth assessment		X	X		
Social support		X	X		
Maternal and paternal antenatal depression and anxiety		X	X		
Maternal and paternal antenatal attachment		X	X		
Maternal and paternal antenatal depression		X	X		
US experiences questionnaire		X	X		
Outcomes: primary and secondary					
Bayley Scales of Infant and Toddler Development, Third Edition					X
Home Screening Questionnaire					X
Mother/father–infant interaction					X
Perinatal and postnatal information				X	
Infant behaviour (crying, sleeping, etc.)				X	
Breastfeeding practices questionnaire				X	X
Maternal and paternal postnatal depression and anxiety				X	X
Social support				X	X
Partner involvement				X	X
Infant growth – weight and length				X	X
Immunisation status				X	X
Clinic attendance				X	X

*GA* gestational age, *US* ultrasound scan

The data collected at each stage is as follows:

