*Baseline at first research ultrasound scan at DPHRU.* Data at the first research visit (< 25 weeks) will include the participant’s contact details, demographic characteristics and reproductive history, socio-economic status, social and instrumental support, and breastfeeding intentions. Maternal and paternal fetal attachment is assessed using the Maternal and Paternal Attachment Scales [44, 45], and the mother and her partner, if available, will complete a social support questionnaire and the Edinburgh Postnatal Depression Scale [46]. The woman and her partner, if available, will also be asked to complete an ultrasound experience questionnaire after the US.
*Six-week postnatal follow-up.* Two trained outcome assessors, blind to the mother’s arm allocation, will complete the follow-up questionnaires with the mothers, infants and partners, where available. Questionnaires will assess perinatal and postnatal information, breastfeeding practices, and partner and social support. Postnatal depression will be assessed for the mother and partner using the Edinburgh Postnatal Depression Scale. Infant growth will be assessed using standard procedures for infant weight and length (the SECA 416 infantometer for length and the SECA 367 infant scale for weight). Measures will be converted to *z*-scores using the 2006 WHO Growth Standards for LAZ, WAZ and WLZ. Birth weight and length as well as key information on maternal and infant birth outcomes will be collected from the infant’s Road to Health Booklet.
*Six-month postnatal follow-up.* Occupational therapists or physiotherapists trained in child development will complete the 6-month follow-up assessments with the mothers, infants and partners, where available. The primary outcome for the 6-month follow-up is child development as measured by the Bayley Scales of Infant and Toddler Development, Third Edition [47].

All of the study outcome measures are presented in Table 2.

**Table 2 Tab2:** Study outcome measures

Outcome	Instrument	Measure	Description	Method of aggregation	Timepoint
Primary outcome					

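### The stated handling of arm numbers does not support the claim of concealed allocation, and the two data collectors at the scan visit also serve as the blinded 6-week assessors

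*Protocol article*

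**What the plan says.** **Allocation.** The Intervention section of the protocol article describes the procedure in three consecutive sentences. "Using computer-generated simple randomisation, each consecutive woman screened will be randomly allocated to a study arm". Then: "Research assistants responsible for screening will receive the study arm numbers for allocation from the study coordinator on a daily basis". Then: "The allocation sequence will be concealed from the research assistants enrolling the participants". The Design section words the unit of allocation differently: "Eligible mothers will be randomised to one of three arms". Table 1 places the eligibility screen, informed consent and random allocation at one enrolment timepoint.

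**Blinding at 6 weeks.** The Data collection section defines the stages as "stage one, baseline at first research ultrasound visit at DPHRU < 25 weeks; stage two, 6-week postnatal follow-up", with stage three at 6 months. It then says: "Data will be collected on tablets at stages one and two by two trained data collectors under the supervision of the study coordinator". The paragraph on the 6-week follow-up says: "Two trained outcome assessors, blind to the mother’s arm allocation, will complete the follow-up questionnaires". Stage three is assigned to other staff, namely occupational therapists or physiotherapists.

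**What differs by arm at the scan visit.** All three arms have a research scan before 25 weeks. Only Arms 2 and 3 hear the child development messages and receive the baby book, printed images and a photograph. Mothers, and partners if available, complete an ultrasound experience questionnaire after the scan.

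**The concern.** Allocation is concealed when the person who judges eligibility and seeks consent cannot know which arm the next woman would enter. Staff who hold the day's arm numbers while they screen may know exactly that. They could then, knowingly or not, decide whom to approach or how hard to persuade according to the next arm. Likely partner attendance and motivation are obvious candidates, and both plausibly bear on the outcomes. Selection of this kind cannot be reliably adjusted away in analysis, and it would affect every comparison between arms.

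The second conflict is narrower. A data collector who takes a post-scan questionnaire from a mother may learn whether she received messages, a book and images. If the same person interviews her at 6 weeks, the assessor may not be blind. Interviewer-collected secondary outcomes such as feeding practices and partner involvement would be the most exposed.

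**Working it through.** The point is procedural, so the check is mainly a comparison of statements.

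**1. Concealment.**
- Who receives arm numbers: the research assistants responsible for screening.
- How often: daily, from the study coordinator.
- From whom the sequence is said to be concealed: the research assistants who enrol.
- Separation in time: none stated. Table 1 has screening, consent and allocation at the same timepoint.
- Safeguard such as a sealed envelope, a central call or release after consent: none described.

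The two sentences are compatible in only two ways. Either the screeners and the enrollers are different people who do not share the numbers, or each number is released singly once consent has been given. The article states neither. Concealing the numbers for later days does not conceal the assignment of the woman being screened now.

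**2. Unit of allocation.** The Intervention section allocates each consecutive woman screened, and the Design section randomises eligible mothers. Taken literally, the former assigns an arm before eligibility and consent are known. The opening of the Intervention section, which randomises on recruitment, and the order of rows in Table 1 favour the Design wording. The sentence about screened women should be aligned with it.

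**3. Blinding at 6 weeks.**
- Stage one is the first research scan visit and stage two is the 6-week follow-up.
- Two data collectors are responsible for both stages.
- Two outcome assessors, called blind, complete the 6-week follow-up.

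Stage-two collection is assigned to the two data collectors, so the natural reading is that they are the two assessors. They therefore also collect data at a visit where the arms are treated visibly differently and where a questionnaire follows the scan. No measure to keep them unaware is described.

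**4. Reach.** At 6 weeks the outcomes in Table 2 are secondary: growth, feeding, depression score, immunisation and clinic attendance, and partner involvement. The Bayley assessment is at 6 months and is done by other staff.

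**5. Sample size.** The stated figure reproduces. For 0.5 SD, 90% power and two-sided 5%, n = 2(1.960 + 1.282)² / 0.5² = 84.06, rounded up to 85 per arm. Then 85 / 0.85 = 100 per arm, and 3 × 100 = 300. Nothing in this point changes these numbers.

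**The case against.** The strongest reply is that foreknowledge is inferred. The article does not say at what time of day the numbers arrive, whether they are masked, or whether they are seen before consent. It uses separate descriptions for assistants who screen and assistants who enrol, and a condensed article may leave release mechanics to the full protocol. This stands to the extent that a breach of concealment cannot be asserted. It does not remove the point, because the article goes beyond silence: it states a mechanism that, as worded, conflicts with the property claimed in the next sentence.

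On blinding, every arm attends a research scan, so meeting a mother there does not reveal her arm. The sonographers deliver the messages, no text places the data collectors in the scan room or says who hands over the book, and the experience questionnaire could be self-completed. Several 6-week measures come from records or instruments. All of this stands, so unblinding is a risk rather than a stated fact.

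A reader might infer more than the documents support:
- **That the 6-month Bayley assessors are unblinded.** The article does not state their blinding, but that is an omission in a condensed text. Supervision by the coordinator does not show that they know the arm.
- **That simple randomisation is an error because it does not guarantee 100 per arm.** It is a legitimate and unpredictable method. The SD of an arm size is √(300 × 1/3 × 2/3) = 8.2. Recruited arms of 92 and 108 give 78.2 and 91.8 evaluable after 15% loss. The standard error is √(1/78.2 + 1/91.8) = 0.1539 SD and power is Φ(0.5/0.1539 − 1.960) = 90.1%, against 90.3% with 85 in each arm.
- **That screeners had wide discretion.** If 300 women were enrolled over seven months, that is 43 a month, or 17% of the stated pool of 250. But that pool is filtered only by gestation, before residence, age, singleton pregnancy, abnormality, morbidity and consent. The Trial status section gives recruitment dates, not numbers.
- **That the false-positive rate is inflated by a known amount.** This needs a bias size that the documents do not give.

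**Conclusion.** The concern holds as two conflicts between stated procedure and stated property. First, the daily supply of arm numbers to screening staff does not support the concealment claim unless a separation of staff or a release after consent applies, and neither is stated. If concealment failed, all outcomes would be affected. Second, the same two data collectors cover the scan visit and the 6-week visit, which puts the stated blinding of the secondary 6-week outcomes at risk. It is not shown to reach the 6-month primary outcome. The mismatch between women screened and eligible mothers is a wording fault that should be corrected with the first conflict.

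No size of bias can be derived from the documents. The conclusion rests on two readings: that numbers supplied daily can be seen before consent, and that the two data collectors of stages one and two are the two 6-week assessors. Both are natural readings, and the trial team can confirm or refute them from its own records.

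**What to change.** **Procedure and wording.** Replace the daily hand-out by release of each assignment, one at a time, only after eligibility and consent have been recorded, either by the coordinator or through REDCap. Say who holds the list. Reword the allocation sentence so that eligible, consenting women are randomised, in line with the Design section.

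**Given that recruitment is complete.** The Trial status section dates the end of recruitment at 30 September 2019, so a new release procedure cannot change who was enrolled. What remains is to establish and report what happened:
- Compare the coordinator's daily lists with the order of enrolment, looking for numbers skipped or used out of order.
- Tabulate women screened, refused and enrolled by arm, as far as an arm was attached at each step.
- State whether screeners and enrollers were the same people and whether the lists were visible before consent. If they were, drop or qualify the concealment claim. A clean tabulation would be reassuring but would not prove concealment.

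**Six weeks.** For visits still to be done, use assessors who did not collect data at the scan visit. For visits already done by the same staff, qualify the blinding claim in the report.

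**Cost.** Wording changes, a check of records that should already exist, and a small reassignment of duties among existing staff. The sample size and the planned models are unaffected.
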